## Abstract

**Background:**

Every year, many infants are infected with the respiratory syncytial virus (RSV) or other agents and need hospitalisation due to bronchiolitis. The disease causes much suffering and high costs. Thus, it is important that the treatment methods are both effective and cost-efficient. The use of different physiotherapy treatment methods is debated, and not all methods are evaluated scientifically. The clinical praxis in Sweden that includes frequent changes of body position and stimulation to physical activity has not previously been evaluated. The aim of this clinical study is to evaluate this praxis.

**Methods:**

This study is a clinical two-centre individually randomised controlled trial (RCT) with three parallel groups. The participants will be randomly assigned to an individualised physiotherapy intervention, a non-individualised intervention, or a control group. All three groups will receive the standard care at the ward, and the two intervention groups will receive additional treatment, including different movements of the body. The primary outcome measure is a clinical index based on determinants for hospitalisation. Baseline assessments will be compared with the assessments after 24 h. The secondary outcome measures include vital signs, the parents’ observations, time spent at the hospital ward, and referrals to an intensive care unit. We also want see if there is any immediate effect of the first intervention, after 20 min.

**Discussion:**

This study will add knowledge about the effect of two physiotherapy interventions that are commonly in use in Swedish hospitals for infants with bronchiolitis or other acute lower respiratory tract infections.

**Trial registration:**

ClinicalTrials.gov NCT03575091. Registered July 2, 2018—retrospectively registered.

## Background

Infants with acute breathing difficulties due to a lower respiratory tract infection such as bronchiolitis or pneumonia often have obstruction of the smaller airways caused by oedema and excess mucus production [1]. This can lead to increased work of breathing with exhaustion of respiratory muscles, feeding difficulties, and increases the risk of developing respiratory distress. Affected infants may need treatment at an intensive care unit (ICU). The hospital care for the children with bronchiolitis involves a high cost for families and health care organisations around the world [2], as this is a common illness in the winter season [3]. The treatment in hospitals is most often supportive, such as supplementing oxygen and fluids [4].

Sometimes, physiotherapy treatment is used to reduce the symptoms of infants who are hospitalised with bronchiolitis. Physiotherapy methods aim at moving and evacuating mucus from the airways in order to reduce work of breathing, increase gas exchange, and increase lung volumes [5–7]. The aim of physiotherapy treatment has also been to reduce time to clinical stability or reduce the duration of a hospital stay [8, 9]. There is no clear consensus about the efficiency of physiotherapy treatment on the whole for this patient group, and some of the treatment methods are questioned or not recommended at all [10, 11].

Many of the physiotherapeutic interventions that are described in international literature for infants hospitalised with breathing difficulties such as bronchiolitis or pneumonia can be described as passive: the physiotherapist places the child in different drainage or resting positions, applies manual pressure to the child’s chest wall, or uses technical devices like continuous positive airway pressure (CPAP) or positive expiratory pressure (PEP) [5, 8, 9, 12–21]. In Sweden, however, physiotherapy for infants in hospital with acute airway infections most often involves stimulation to physical activity and frequent changes of the body position combined with other methods [22]. This praxis is supported by general physiological principles of the positive effect on lung function of the change of body positions and physical activity [23–25], but these methods have not been evaluated scientifically for this patient group before, and that is why this study was designed.

There are studies that indicate a positive effect of prone position (lying on their stomach) for children with respiratory problems. Most of these studies, however, are made on premature infants who are mechanically ventilated [26, 27]. The present study aims at investigating changes of body position on full-term children who breathe spontaneously.

## Methods/design

### Aim

The present study protocol describes a randomised control trial that aims to compare the effect of an individualised physiotherapy intervention, a non-individualised intervention and a control group receiving standard care, in hospitalised infants 0–24 months of age.

### Study design

This is a clinical two-centre individually randomised controlled trial with three parallel groups.

We plan to include 162 infants who will be randomised to either the individualised physiotherapy intervention group, the non-individualised intervention group, or the control group, 54 in each group. In the flow chart (Fig. 1) and in the Standard Protocol Items: Recommendations for Interventional Trials (SPIRIT) figure (Fig. 2), the overall study design is described, which is in agreement with the SPIRIT 2013 checklist (see Additional file 1). Any significant changes of the protocol will be registered at ClinicalTrials.gov and communicated to the staff involved through the contact staff on the both sites.

**Fig. 1 Fig1:**
[figure not shown]
Flow chart of the study design

**Fig. 2 Fig2:**
[figure not shown]
The SPIRIT figure of enrolment, interventions, assessments, and outcomes

### Setting

The study will take place at the children’s wards in two hospitals in the south of Sweden (Malmö and Växjö). One hospital has a catchment area of about 500,000 inhabitants, the other of about 100,000 inhabitants. The two hospitals are situated about 200 km apart.

### Inclusion of participants

Potential participants will be identified and recruited by the staff in the paediatric wards. Inclusion criteria are as follows: age 0–24 months, hospitalised on the basis of acute airway infection, born in gestational week 35 or later. Patients must be included within 24 h of hospital admission. At least one of the parents/guardians needs to understand written Swedish, English, Arabic, or Persian. Exclusion criteria are as follows: previous respiratory or cardiac diagnoses.

To include adequate participants, the study will be mentioned at two pulse meetings a day in the wards, and all staff members will be trained in the study design. Some staff members will get additional training to support their colleagues. The main investigator will regularly visit the wards in person and will have telephone communication in between the visits to remind the staff and to answer questions.

First, the parents will receive written information about the study (text in Swedish, Arabic, English, or Persian). At that time and when they have had the opportunity to read the information, they may ask questions and get additional information from the staff. In order to admit their child into the study, the parent/s will sign a written consent form. The participation in the study will end when the infant is either discharged to the home or referred to an intensive care unit or if the parents decide to withdraw the participation of their child.

### Randomisation

When a child is included in the study, it will be individually randomised to one of the three groups. A statistician who is independent of the study has performed randomisation in blocks, stratified by the two sites. The statistician prepared sealed paper envelopes, numbered in sequence, that are kept in a locked safe accessible only for the researchers responsible for the study. A small number of envelopes will be brought to the study binders at the two hospital wards when needed. The staff that will include an infant in the study after parental consent is instructed to open the envelope with the lowest number, which will be the top envelope in the binder.

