### Outcome measures and assessors

#### Baseline data

Participant characteristics will be collected from (i) interview with parents (heredity for atopic diseases, passive smoking habits, duration of the infection) and (ii) medical record (gender, age, possible viral agent: respiratory syncytial virus or influenza).

To collect the main data, the nursing staff will make a clinical assessment at study start (t1) and the second assessment 20 min later (t2), following directly after the intervention/interval. See also Fig. 1. The same person will perform these two assessments. The following assessments will be performed every three hours for the rest of the infant’s hospital stay. They will be performed by the clinical staff available at that time. In the intervention groups, it will be a different member of staff who will perform the intervention from the one who makes the first two assessments. All members of the staff will be trained on how to perform the assessments, which in many aspects are identical to the standard protocol at the ward. Once daily, the clinical staff will report if the infant has received any inhalations (in which case the medical record is scanned for more information on this) and also if the infant is actively moving about in the room or not. See Additional file 2 for the assessment protocol in Swedish.

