#### Secondary outcome measures

The clinical status of the participants will be assessed by the nursing staff and the parents using the measures in Table 2. Wang score [31] is an observational scale where the nursing staff scores the infants 0–3 where 3 is most severe. The scoring system includes respiratory rate, wheezing, retractions/nasal flaring, and general condition. It has been validated in clinical studies [31–33]. The respiratory rate, retractions, and wheezing is commonly used in studies of bronchiolitis, and the inter-observer agreement is good: 93.1% with a weighted kappa of 0.72 (95% CI 0.66–0.78) [33].

**Table 2 Tab2:** The secondary outcome measures, reported by the clinical staff unless otherwise stated

Secondary outcome	Measure	Registration time
Wang respiratory score [31]		
Respiratory rate	Manual count, per minute. Scale 0–3 where 3 is worst	At baseline, 20 min later and every 3rd hour
Wheezing sound	Clinical observation. Scale 0–3 where 3 is worst	At baseline, 20 min later and every 3rd hour
Retractions/nasal flaring	Clinical observation. Scale 0–3 where 3 is worst	At baseline, 20 min later and every 3rd hour
General condition	Clinical observation. Scale 0–3 where 3 is worst	At baseline, 20 min later and every 3rd hour
General condition (parents’ report)	Observation. Scale 0–10 where 10 is worst	At baseline, 20 min later and every 3rd hour during daytime
Food intake (parents’ report)	Observation. Scale 0–2 where 2 is worst	At baseline, 20 min later and every 3rd hour during daytime
Body weight	Naked weight on scales, g	Once daily
Heart rate	Counts per minute, by pulse-oximetry, probe on the foot	At baseline, 20 min later and every 3rd hour
Time to recovery	Time at hospital, hours	At the end of the study
Lung complications	Referral to intensive care unit—yes/no	At the end of the study

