#### Interventions

The position for all infants at baseline is supine on the bed, that is, lying on their backs. Directly following the baseline assessment, there will be 20 min of interventions for the two intervention groups and 20 min of no extra intervention for the controls. All participants will receive the standard care at the ward without limitation, and the participants in the intervention groups will have physiotherapy treatment in addition to the standard care.

*The standard care* at the wards is information to the parents about the importance of fluid intake for their infant, oxygen supplementation, nose drops and suctioning, high nasal flow, inhalations, fluid supplementation, and analgesics, according to need.

The different interventions were chosen based on what is routinely carried out by physiotherapists or nursing staff in hospitals in Sweden [22], including an individualised physiotherapy treatment and a reduced non-individualised treatment. We expect that the individual intervention might be more efficient, but at the same time want to know whether the non-individualised treatment would be sufficient for these patients, indicated by outcomes in the non-individualised group showing a both statistically and clinically relevant improvement compared to the control arm.

In the individualised intervention group, the intervention is minimally given once daily by the physiotherapist, and in the non-individualised intervention group, the intervention is minimally given by the staff once. The randomised treatment, or indeed what will be performed in the control group, will not be monitored, so there might be differences in adherence to the interventions between parents. Our intention, however, is to evaluate the current practice that includes instructions and encouragements to the parents. This attitude is in accordance with a so-called pragmatic RCT, as our intention is to apply the results to the usual care setting [39].

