#### Statistical and sample size calculations

Descriptive statistics will be shown as mean with standard deviation or median with minimum and maximum values for continuous and ordinal variables where appropriate. Number with percent will be shown for categorical variables.

The primary outcome is clinical index at 24 h. The time is chosen since our experience is that most infants will remain at hospital at that time and an effect should have been shown. The effect of the individualised physiotherapy intervention, the non-individualised intervention, and a control group receiving standard care on clinical index at 24 h will be assessed by an ANCOVA model with adjustment for baseline clinical index, and post hoc test for the different group combinations will be performed.

The secondary outcomes, including clinical index at 20 min, will first be assessed by an overall test and if the overall test is shown significant post-hoc tests will be performed. A *p* value below 0.05 will be considered significant for the overall test. Continuous and ordinal variables will be assessed by ANCOVA model with adjustment for baseline values where possible, ANOVA, or Kruskal-Wallis test, with *t* test or Mann-Whitney *U* test as post hoc tests, where appropriate. Categorical variables will be assessed by Fisher’s exact test. Explorative subgroup analyses by gender will be performed. To increase the knowledge about what time the infants will recover, data are collected every 3 h. We will analyse the time the infants recover by means of Fisher’ exact test and Kaplan-Meier analysis. IBM SPSS Statistics 24, or higher, Windows (IBM Corporation, Armonk, NY, USA) will be used to perform the statistical analyses.

The primary analysis will include all participants with available outcome data at 24 h. Drop-outs will not be included in this analysis. A dataset with the imputed values might also be analysed. Simple imputation, mean of the value before and after the missing value or last value carried forward from the assessment three hours earlier, will be performed if data is missing at hour 24 and the patient is still at hospital. If an infant will be discharged from the ward before hour 24, that participant will be excluded from this analysis and will be analysed in the same way as the other potential drop-outs.

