## Discussion

Infants hospitalised due to acute respiratory failure caused by bronchiolitis and pneumonia is a recurring group of patients in paediatric departments. Hospitalisation is a burden for both the families and for society, and possible treatments that reduce the need for hospitalisation by reducing the work of breathing and increase the general condition of the infant are called for, as well as finding treatments that alleviate the current situation for these infants during hospitalisation.

Our study focuses on a possible effect of an individualised physiotherapy intervention and a non-individualised intervention compared to the standard care (without additional movements).

We chose to include infants without previously diagnosed respiratory and cardiac diseases, in order to evaluate the effect of physiotherapy in a homogenous group of patients, in a real-life setting in two departments.

We chose the individualised physiotherapy intervention because that is the most common physiotherapy treatment method in Sweden [22] and previously not evaluated. The non-individualised physiotherapy intervention can be used by the nursing staff and is less time-consuming and often used, while the control group will receive treatment as recommended in earlier studies [4, 40].

Blinding a physiotherapy study is difficult. In some studies, this problem was solved by bringing all infants to a closed room to do the physiotherapy intervention or nothing, without the parents and nursing staff knowing what was done [5, 8, 19]. In our study, we wanted to evaluate the commonly used methods that often involve parents’ actions, and blinding of parents to participants, care providers, or assessors was not possible due to the nature of the intervention. To minimise possible bias, one person will perform the intervention and another person will evaluate the result of the different interventions (make the assessment). The statistician involved in the analyses will be blinded.

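### As the text most naturally reads, the envelope is opened before baseline, so the t1 assessor and the parents can know the arm when they give subjective baseline ratings

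*Protocol article*

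**What the plan says.** All references are to the Protocol article.

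- **Randomisation.** Allocation comes at inclusion: "When a child is included in the study, it will be individually randomised to one of the three groups". It is carried out on the ward: "The staff that will include an infant in the study after parental consent is instructed to open the envelope with the lowest number".
- **Baseline data.** Nursing staff make the t1 assessment at the start of the study. The same person repeats it 20 minutes later (t2). For the two treated arms the rule is: "it will be a different member of staff who will perform the intervention from the one who makes the first two assessments".
- **Interventions.** There is no gap after t1: "Directly following the baseline assessment, there will be 20 min of interventions for the two intervention groups". Controls have 20 minutes without extra intervention.
- **Secondary outcome measures, Table 2.** Parents rate general condition (0–10) and food intake (0–2) "At baseline, 20 min later and every 3rd hour during daytime". Staff score respiratory rate, wheezing, retractions/nasal flaring and general condition (0–3 each) at baseline too.
- **Statistical and sample size calculations.** The primary analysis is an "ANCOVA model with adjustment for baseline clinical index". Continuous and ordinal secondary outcomes, including the index at 20 minutes, are also adjusted for baseline where possible.
- **Discussion.** Blinding of participants, "care providers, or assessors was not possible due to the nature of the intervention". The safeguard offered is that one person treats and another assesses.

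**The concern.** ANCOVA relies on a covariate that allocation has not influenced. If the t1 assessor or the parents know the arm, a subjective baseline rating can shift with it, and the adjustment carries part of that shift into the estimated effect. On a scale where higher is worse, a treated arm rated too ill at t1 appears to improve more than it did.

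The reason given for not blinding assessors is the nature of the intervention. At t1 no intervention has taken place, so that reason does not cover this assessment. Having one person treat and another assess does not hide the arm from the assessor either.

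The 20-minute comparison is the most exposed, because one person scores both t1 and t2.

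**Working it through.** **Order of steps, from the text**

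1. Randomisation is tied to inclusion, and the envelope is opened after consent. No passage makes t1 a step before opening.
2. Treatment starts directly after t1. It is given by a physiotherapist in one arm and by ward staff in another, so someone will usually have arranged the right person by then.
3. The rule that treater and assessor must differ is stated only for the intervention groups. This also suggests that the arm is known when t1 is staffed.
4. No passage says that the t1 assessor or the parents are kept unaware of the arm, or that their ratings are recorded first.

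This makes envelope before t1 the natural reading. It remains an inference.

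**The plan's own figures**

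Inputs: difference 2, SD 2.8, two-sided alpha 0.016, power 0.80, dropout 20%. The two-sample t test (noncentral t) needs 43 per group, with power 0.801. Then 43 / 0.8 = 53.75, rounded up to 54, and 3 × 54 = 162. The figures reproduce, and the order of envelope and t1 does not enter them.

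**Possible bias, parents' 0–10 rating**

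Adjusted difference = (follow-up difference) − slope × (baseline difference). An arm-related baseline shift b therefore adds a bias of size slope × b. Neither quantity is in the documents. Assume a slope of 0.5 to 0.8 and b of 0.5 to 1 point:

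- low: 0.5 × 0.5 = 0.25 points
- high: 0.8 × 1.0 = 0.8 points

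**Possible bias, primary index (illustration only)**

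Assume a baseline–24 h correlation r of 0.3 to 0.7, equal SDs (so slope = r), and b of 0.25 to 1.0 index points. The residual SD is 2.8 × √(1 − r²), the standard error is that times √(2/43), and the critical value for 0.016 is 2.409.

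| r | b | Bias = r × b | Share of 2 points | Type I error per comparison |
|---|---|---|---|---|
| 0.3 | 0.25 | 0.075 | 4% | 0.017 |
| 0.5 | 0.5 | 0.25 | 12.5% | 0.029 |
| 0.7 | 1.0 | 0.70 | 35% | 0.22 |

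Middle row: residual SD 2.8 × √0.75 = 2.425; standard error 2.425 × √(2/43) = 0.523; 0.25 / 0.523 = 0.478; type I error = 1 − Φ(2.409 − 0.478) + Φ(−2.409 − 0.478) = 0.029.

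The last row is not a realistic expectation. An average shift of 1 point means about one full category misrecorded per infant, on items that are pulse-oximetry readings, oxygen concentration or flow settings. Table 1 registers oral intake, worth 3 of the 11 points, at feeding sessions and not as a t1 observation.

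**The case against.** **The order is not stated.** A reader might infer as fact that baseline is scored with the arm known. The text does not say so. Opening after consent is compatible with opening after t1, and Figs 1 and 2, which may show the order, are not available. A treater who is ready directly after t1 does not mean that the assessor or the parents know the arm. This stands, and the point is therefore that they *can* know it.

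**The primary outcome is hardly touched.** A reader might infer that the primary ANCOVA is compromised. The index was built from items that the plan describes as objective, and at t1 they are mostly instrument readings or device settings. This stands too.

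**The direction is unknown, and follow-up stays open.** Raters who lean the same way at t1 and later produce errors that partly cancel under adjustment, and concealing t1 alone removes that offset. Later ratings remain unblinded, and their error enters at full weight. This also stands: the change secures the covariate and does not cure follow-up bias.

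**Further inferences that the documents do not support.** A reader might infer that drop-outs would lack a severity measure. The sample size section already compares them on saturation, respiratory rate and heart rate at admission. A reader might also infer that hour 24 falls later in the illness in the individualised arm because t1 waits for a physiotherapist. The Discussion expects physiotherapist absence to lead to exclusions, but no passage describes a delayed t1. Starting the clock at envelope opening, with a looser link between t1 and treatment, could itself make the t1–t2 interval and the 24-hour window differ by arm.

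**Conclusion.** The point holds as an inexpensive improvement. On the natural reading, the t1 assessor and the parents can know the arm when they rate baseline, and nothing in the article prevents it. Whatever the missing figures show, the Discussion's blanket reason for not blinding assessors does not cover t1.

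The exposure is mainly in the parents' general condition and food intake ratings and in observed wheezing, retractions and general condition, most of all at 20 minutes. For the parents' 0–10 rating, the bias would be 0.25 to 0.8 points under the assumed slope and shift; its direction cannot be known from the documents. The effect on the primary index is likely small. The sample size of 43 evaluable per group and 162 in total is unaffected.

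**What to change.** **Randomisation and Baseline data.** Require the staff and parent t1 ratings to be completed and written down before the arm is disclosed to the t1 assessor and the parents. Either of two arrangements would do this:

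- open the envelope after t1 has been recorded; or
- have another staff member open it and arrange the treater, while the t1 assessor and the parents stay unaware until their ratings are recorded.

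In all arms, the intervention or control interval should still follow t1 directly, as the Interventions section has it, so that the t1–t2 interval stays the same.

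**Discussion.** State that baseline is assessed before the arm is disclosed, and limit the statement that blinding was impossible to assessments after the intervention has begun.

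**Cost.** One procedural sentence and a line in staff training. There is a small burden: a treater must be reachable at inclusion, or a second staff member must handle the envelope. Recruitment began in November 2017, so a change of practice helps only infants still to be included. If the wards already work this way, one sentence saying so settles the point.
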